**2.3 Rationale**

The *RAS/BRAF/MEK/MAPK* pathway is one of the cell’s major pathways for transmitting extracellular growth factor signals to the nucleus. Signaling via this pathway upregulates Cyclin D**1, which binds to the CDK4/6 kinase, promoting phosphorylation of the retinoblastoma tumor suppressor protein (RB). Phosphorylation of RB releases it from members of the E2F family of transcription factors, allowing the activation of genes required for cells to progress from the G1 to S phase of the cell cycle.** Activating mutations in any of the kinases in the pathway would be expected to result in uncontrolled cell proliferation. *RAS* mutations are found at high frequency in some cancers (e.g. colon); however they are uncommon in most melanomas. The low frequency of *RAS* mutation in melanoma suggests that activation of the MAPK pathway may be accomplished by activating downstream elements. Our group has recently reported that activating *BRAF* mutations occurs in 48% of metastatic melanoma tissues (30). Other groups have reported frequencies of 21-67% of melanomas tested. All of the *BRA*F mutations occur in exons 11 or 15 which correspond to the G-loop and the activation segment of the kinase domain, respectively. Approximately 90% of *BRAF* mutations in melanoma are found at amino acid 599 (exon 15), constituting a mutational hotspot. The mutations produce a constitutively activated kinase, which, when transfected into fibroblasts, leads to cell transformation. In this trial, we propose to test an anti-*BRAF* drug BAY 43-9006. This drug directly inhibits RAF function; however, its specificity for this kinase is not yet established. Although the results of Phase I clinical trials have only been reported in abstract form, it appears that the drug can be administered safely using a weekly dosing schedule. To date, there is little information on whether this compound inhibits phosphorylated MAPK, and no data exist on the response of melanoma patients or other patients with tumors expressing activated *BRAF* mutation.

**3. PATIENT SELECTION**

**3.1 Eligibility Criteria (Appendix A)**

3.1.1 Patients must have histologically or cytologically confirmedunresectable Stage III and Stage IV melanoma. The first 13 patients in each subgroup must have melanoma tumors amenable to biopsy before and after therapy and they must consent to having these biopsies done. These biopsies are necessary in order to carry out the correlative pharmacodynamic measurements (see below). In most cases, biopsied tumors will be cutaneous or subcutaneous metastases. If additional patients are accrued beyond the first 13- patients in each subgroup, we will obtain either real time biopsies or paraffin embedded tissue from a previous biopsy for prospective identification of the B-RAF mutation. This is necessary in order to subgroup patients. Since there has been a preponderance of wild type patients accrued to date, the protocol will allow enrollment to any patient with or without biopsy accessible metastatic disease in an attempt to expediciously complete the trial.

3.1.2 Patients must have measurable disease, defined as at least one lesion that can be accurately measured in at least one dimension (longest diameter to be recorded) as >20 mm with conventional techniques or as >10 mm with spiral CT scan. See section 9.1.1 for the evaluation of measurable disease.

3.1.3 No prior systemic chemotherapy for metastatic disease is permitted.

3.1.4 Age 18 years.

3.1.5 Life expectancy 3 months.

3.1.6 ECOG performance status 0-2 / Karnofsky 60% (see **Appendix B**).

3.1.7 No minimum period since last therapy is defined, but patients must have adequate organ function not toxicity as defined in 3.1.8, and preexisting non-hematological dysfunction <grade 2.

3.1.8 Patients must have normal organ and marrow function as defined below:

- absolute neutrophil count 1.5 x 109/l
- platelets 100 x 109/l
- total bilirubin < 2 x upper limit of normal
- AST (SGOT) / ALT (SGPT) 2.5 x upper limit of normal
- creatinine 1.5 x upper limit of normal

3.1.9 Patients with known brain metastases may be included in this study if they fulfill all of the following criteria:

- the lesions have remained radiologically stable for at least six weeks after completion whole brain irradiation, and remain stable at the time of study entry
- there is no mass effect present radiologically
- the patient is no longer receiving steroids to control symptoms of brain metastases

3.1.10 Ability to understand and the willingness to sign a written informed consent document.

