**Subgroup A: No prior therapy, B-RAF+**

These patients have had no prior therapy and their melanoma tumors have a *BRAF* mutation.

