**Subgroup B: No prior therapy, B-RAF-**

These patients have had no prior therapy and their tumors do not have a *BRAF* mutation (wild BRAF status).

B-RAF status can be determined from real-time biopsies or paraffin-embedded metastatic tumor obtained previously. The first 13 patients in each subgroup must have melanoma metastases amenable to biopsy before and after therapy and must consent to having these biopsies done.

**. Since there has been a preponderance of wild type patients accrued to date, the protocol will allow enrollment to any patient with or without biopsy accessible metastatic disease in an attempt to expediciously complete the trial.

All patients will receive continuous Bay 43-9006 400mg po BID. Efficacy will be evaluated in terms of measurable anti-tumor effects and proportion of clinical responses. Correlation of response with presence of BRAF mutation in the melanoma tumor will be determined and the hypothesis that treatment with BAY 43-9006 can disrupt the MAPK pathway by down regulating downstream proteins such as phosphor-ERK, CDK4, and cyclin D1 will be explored.

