## 2.1.2 Immunotherapy

Interest in the use of biologic response modifiers has been fostered by a variety of clinical and laboratory observations suggesting that host immunologic mechanisms may occasionally influence the course of melanoma. During the past decade, two biologic agents, interferon- (IFN-) and IL-2, have shown reproducible single agent anti-tumor activity against advanced melanoma. Both IL-2 and IFN- have produced response rates in the 15 to 20% range (10,11). High dose IL-2 therapy, administered by intravenous bolus either alone or in combination with LAK cells, has produced durable complete responses in approximately 5% of patients (11-14). However, the known adverse effects of IL-2 have precluded wide application due to the increasedrisk of treatment-related morbidity.

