**3.2 Exclusion Criteria**

3.2.1 Patients with prior chemotherapy for metastatic melanoma.

3.2.2 Patients receiving any other investigational agents.

3.2.3 Uncontrolled intercurrent illness including, but not limited to, ongoing or active infection, uncontrolled hypertension, symptomatic congestive heart failure, unstable angina pectoris, cardiac arrhythmia, or psychiatric illness that would limit compliance with study requirements.

- - 1. Pregnant women are excluded from this study because the teratogenic or abortifacient effects of BAY 43-9006 are unknown.Women who are breastfeeding are not eligible or they must stop breastfeeding because of the unknown risk for adverse events in nursing infants.
    2. Patients with a history of serious allergic reactions to eggs (BAY 43-9006 is formulated using egg phospholipid).

3.2.6 Patients having any evidence of a bleeding diathesis. Patients on therapeutic anti-coagulation must have a weekly monitored PT/INR during the first cycle, then monitored closely thereafter as deemed necessary by the treating physician.

3.2.7 Patients who cannot swallow pills for whatever reason will be excluded.

3.2.8 HIV-positive patients receiving combination anti-retroviral therapy are excluded because of possible pharmacokinetic interactions with the investigational agent.

3.2.9 Patients with prior malignancies, except for adequately treated basal or squamous cell skin cancer, adequately treated non-invasive carcinomas or other cancers from which the patient has been disease-free for > 5 years.

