**9.1.1 Measurable disease**

Measurable lesions are defined as those that can be accurately measured in at least one dimension (longest diameter to be recorded) as 20 mm with conventional techniques (PET, CT, MRI, x-ray) or as 10 mm with spiral CT scan. All tumor measurements must be recorded in millimeters.

**Note:** Tumor lesions that are situated in a previously irradiated area will be considered measurable only if there has been documented progression of the lesion since completion of radiotherapy.

Clinical lesions

Clinical lesions will only be considered measurable when they are superficial (e.g., skin nodules and palpable lymph nodes). In the case of skin lesions, documentation by color photography, including a ruler to estimate the size of the lesion, is recommended.

Chest x-ray

Lesions on chest x-ray are acceptable as measurable lesions when they are clearly defined and surrounded by aerated lung. However, CT is preferable.

Conventional CT and MRI

These techniques should be performed with cuts of 10 mm or less in slice thickness contiguously. Spiral CT should be performed using a 5 mm contiguous reconstruction algorithm. This applies to tumors of the chest, abdomen, and pelvis. Head and neck tumors and those of extremities usually require specific protocols.

Ultrasound (US)

When the primary endpoint of the study is objective response evaluation, US should not be used to measure tumor lesions. It is, however, a possible alternative to clinical measurements of superficial palpable lymph nodes, subcutaneous lesions, and thyroid nodules. US might also be useful to confirm the complete disappearance of superficial lesions usually assessed by clinical examination.

Endoscopy, Laparoscopy

The utilization of these techniques for objective tumor evaluation has not yet been fully and widely validated. Their uses in this specific context require sophisticated equipment and a high level of expertise that may only be available in some centers. Therefore, the utilization of such techniques for objective tumor response should be restricted to validation purposes in reference centers. However, such techniques may be useful to confirm complete pathological response when biopsies are obtained.

Cytology, Histology

These techniques can be used to differentiate between partial responses (PR) and complete responses (CR) in rare cases (e.g., residual lesions in tumor types, such as germ cell tumors, where known residual benign tumors can remain).

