# ON-STUDY REGISTRATION

| NYU 04- A Phase II Study of BAY 43-9007 in Stage IV Malignant Melanoma | | | |
| --- | --- | --- | --- |
| Date Submitted:  Mo / Dy / Yr ___/ ___/ ___ | NCI Protocol #: | Patient Initials: | |
| SEX:  [ ] M [ ] F | Date of Birth:  Day/ Mon / Yr  ___/ ____/ ___ | Age (yrs) | Ethnicity: |
| Body Weight (Kg) | | Height (cm) | |
| Method of Payment: | | Postal Code: | |
| Histology:  **Melanoma** | | Performance Status: | |
| Date of Diagnosis:  Mo / Dy / Yr: _____/ _____/ _____ | | Date On-Study:  Mo / Dy / Yr: _____/ _____/ _____ | |
| Prior Therapy  Chemo [ ] Y [ ] N Hormone [ ] Y [ ] N Immuno [ ] Y [ ] N  Radiation [ ] Y [ ] N Surgery [ ] Y [ ] N | | | |

Patient ID Number: _________________ (assigned at Coordinating Center)

Completed By:

Name: ____________________ Signature: ___________________ Date: ___/ ___/ ___

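### Section 3 sets no interval since prior therapy and bars only chemotherapy, while the Schema and Appendix A say no prior therapy; under Section 3, carried-over shrinkage could count as response

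*Protocol*

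**What the plan says.** Section 3.1.7 of the protocol: "No minimum period since last therapy is defined, but patients must have adequate organ function". Its only other conditions concern toxicity and existing organ dysfunction.

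Two places in Section 3 restrict earlier treatment, and both name chemotherapy only: 3.1.3, "No prior systemic chemotherapy for metastatic disease is permitted", and 3.2.1, which excludes "Patients with prior chemotherapy for metastatic melanoma". Section 3.2.2 covers patients currently on other investigational agents, and 4.1.1 covers other anticancer treatment given during the study. Neither reaches treatment that ended just before day 1.

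The Schema is stricter. Subgroup A: "These patients have had no prior therapy and their melanoma tumors have a" BRAF mutation. Subgroup B: "These patients have had no prior therapy and their tumors do not have a" BRAF mutation. The Appendix A checklist likewise has a line for no prior therapy.

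The registration form in Appendix G offers "Chemo [ ] Y [ ] N Hormone [ ] Y [ ] N Immuno [ ] Y [ ] N" under prior therapy, with no date of last treatment.

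For irradiated areas, Section 9.1.1 says that lesions "will be considered measurable only if there has been documented progression of the lesion since completion of radiotherapy". No matching rule exists for systemic treatment. Baseline scans may be up to 4 weeks old (Sections 8 and 9.2), and response is measured against the baseline sum of diameters (9.1.3, 9.3.1).

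**The concern.** There is no control arm, so the response rate in each BRAF subgroup is read directly as the activity of BAY 43-9006. That reading needs tumours that are not already shrinking from something else.

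Section 3.1.7 protects safety, through organ function, but does not protect attribution. Under Section 3 a patient could have a baseline scan before or during IL-2 or interferon, stop, start study drug within days and be scored on day 56 against that scan. Both treatments would contribute to the change. Section 2.1.2 says that these two agents "have produced response rates in the 15 to 20% range", so prior immunotherapy can produce responses.

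The decision rule leaves little room. One response in the first 13 patients opens stage 2, and a fifth response among 37 accepts the drug for that subgroup.

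**Working it through.** **Step 1. Who can enter, text by text**

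| Source | Bar on earlier treatment | Recent IL-2 or interferon |
|---|---|---|
| 3.1.3, 3.2.1 | Chemotherapy for metastatic disease | Not barred |
| 3.1.7 | No minimum interval | Not barred |
| 3.2.2, 4.1.1 | Concurrent agents only | Not barred once stopped |
| Schema, both subgroups | Any prior therapy | Barred |
| Appendix A checklist | Any prior therapy | Barred |

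The stricter wording cannot be fully literal. Appendix A itself admits patients after whole brain radiation, as does 3.1.9. Section 3.1.7 would have nothing to govern if no patient had earlier treatment. The limit to metastatic disease in 3.1.3 and 3.2.1 would be redundant if everything were barred. The document therefore does not settle the question.

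**Step 2. Reproduce the stated error rates (Section 11.2)**

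Inputs: 13 patients in stage 1, stop at 0 responses; 37 in total, reject the drug at 4 or fewer; null rate 0.05, alternative 0.20.

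P(accept | p) = Σ over x = 1 to 13 of P[Bin(13, p) = x] × P[Bin(24, p) ≥ 5 − x]

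- p = 0.05: 0.0329, stated as 3.3%.
- p = 0.20: 0.8583, so the type II error is 1 − 0.8583 = 0.1417, stated as 14.2%.
- Passing stage 1 at p = 0.05: 1 − 0.95^13 = 1 − 0.513 = 48.7%.

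Both stated figures reproduce.

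**Step 3. Effect of carry-over on an inactive drug**

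Assumptions, neither given in the document: a share f of patients enters soon after immunotherapy, and each of these has probability q of a carried-over response after baseline. The true drug rate is 5%. The apparent rate is

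p* = (1 − f) × 0.05 + f × [1 − 0.95 × (1 − q)] = 0.05 + 0.95 × f × q

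| f | q | p* | False-positive rate | Pass stage 1 |
|---|---|---|---|---|
| 0 | – | 5.00% | 3.3% | 48.7% |
| 5% | 5% | 5.24% | 3.9% | 50.3% |
| 10% | 5% | 5.48% | 4.6% | 51.9% |
| 10% | 10% | 5.95% | 6.1% | 55.0% |
| 20% | 10% | 6.90% | 10.0% | 60.5% |
| 20% | 15% | 7.85% | 14.9% | 65.5% |
| 20% | 20% | 8.80% | 20.7% | 69.8% |

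The last two rows treat the whole published response rate to immunotherapy as carry-over. They are upper bounds for q, not estimates. Solving P(accept | p*) = 0.05 gives p* of about 5.62%, so the 5% target is crossed when f × q exceeds (0.0562 − 0.05) / 0.95, about 0.65%.

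**Step 4. Fragility without f and q**

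Suppose exactly one carried-over responder is among the first 13 and the other 36 patients respond at 5%. Stage 1 then passes with certainty, and acceptance needs 4 or more of 36: P[Bin(36, 0.05) ≥ 4] = 10.4%. This is conditional on such a patient existing and says nothing about how likely that is.

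**The case against.** The strongest objection is that the premise is contested by the protocol itself. The Schema and Appendix A say no prior therapy, the heading of Section 3.1 points to Appendix A, and Section 10.1 requires an eligibility checklist and central verification. If those texts govern, f = 0 and no carry-over from immunotherapy arises. A reader might infer from 3.1.3 and 3.1.7 that prior immunotherapy is knowingly permitted. The document does not support that as a fact; it supports only that Section 3 permits it and other pages do not. The registration form does not decide the matter, because it also has a box for chemotherapy, which is barred for metastatic disease.

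The words on last therapy in 3.1.7 may also refer to adjuvant treatment, surgery or radiotherapy. That is a fair reading, but the sentence is not limited to it.

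Several provisions narrow the route. Shrinkage before the baseline scan is already in the baseline, so a counted response needs a further 30% fall. Responses must be confirmed at least 4 weeks later (9.4.1). Baseline is to be as near to treatment start as possible (9.2). Independent review covers patient files as well as images (9.6). These make carry-over less likely, but none requires progression after earlier systemic treatment.

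A reader might also set the 15 to 20% for IL-2 and interferon beside the 20% alternative and conclude that carry-over could mimic an active drug. That does not follow. The figure is the response rate to those treatments when given, not the chance of a late response first appearing after a new baseline, and it would have to apply in full to nearly every patient.

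**Conclusion.** The concern stands in a limited form. Section 3.1.7 expressly sets no interval since last therapy. Together with the chemotherapy-only bars, this lets Section 3 admit patients just off IL-2 or interferon without documented progression, while the Schema and Appendix A say otherwise. Under Section 3, carried-over shrinkage could enter the primary endpoint of an uncontrolled trial.

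The size is unknown. With small assumed values (f = q = 5%, or f = 10% and q = 5%) the false-positive rate stays within the protocol's 5% target; from f = q = 10% upward it does not. These figures rest wholly on the assumed f and q and on a true drug rate of 5%. They show how sensitive the decision rule is and are not an estimate of actual bias. The two-stage design and its stated error rates are not in error. The change should be made because it is cheap and bears directly on the primary endpoint.

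**What to change.** Reconcile the Schema and Appendix A with Sections 3.1.3, 3.1.7 and 3.2.1, so that one statement of permitted earlier treatment applies throughout.

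- If no prior systemic therapy is intended, say so in Section 3 and limit 3.1.7 to the treatments that remain possible.
- If prior immunotherapy is intended to be allowed, amend 3.1.7 along the lines of 9.1.1: earlier systemic therapy is complete before the baseline scan, and progression since then is documented before entry. Whether to add a minimum interval, and its length, is for the sponsor to decide. Align the Schema and Appendix A accordingly.

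Under the second option, add the date of last prior therapy to the registration form beside the existing boxes.

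The cost is one amendment to the eligibility text and, under the second option, one form field. Some recently treated patients may be deferred or need a later baseline scan, which slows accrual slightly.

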**3.2 Exclusion Criteria**

3.2.1 Patients with prior chemotherapy for metastatic melanoma.

3.2.2 Patients receiving any other investigational agents.

3.2.3 Uncontrolled intercurrent illness including, but not limited to, ongoing or active infection, uncontrolled hypertension, symptomatic congestive heart failure, unstable angina pectoris, cardiac arrhythmia, or psychiatric illness that would limit compliance with study requirements.

- - 1. Pregnant women are excluded from this study because the teratogenic or abortifacient effects of BAY 43-9006 are unknown.Women who are breastfeeding are not eligible or they must stop breastfeeding because of the unknown risk for adverse events in nursing infants.
    2. Patients with a history of serious allergic reactions to eggs (BAY 43-9006 is formulated using egg phospholipid).

3.2.6 Patients having any evidence of a bleeding diathesis. Patients on therapeutic anti-coagulation must have a weekly monitored PT/INR during the first cycle, then monitored closely thereafter as deemed necessary by the treating physician.

3.2.7 Patients who cannot swallow pills for whatever reason will be excluded.

3.2.8 HIV-positive patients receiving combination anti-retroviral therapy are excluded because of possible pharmacokinetic interactions with the investigational agent.

3.2.9 Patients with prior malignancies, except for adequately treated basal or squamous cell skin cancer, adequately treated non-invasive carcinomas or other cancers from which the patient has been disease-free for > 5 years.

**3.3 Inclusion of Women and Minorities**

*Both men and women and members of all ethnic groups are eligible for this trial, although accrual of non-white patients is expected to be low as melanoma is rare in non-white ethnic groups. Based on accrual in previous melanoma studies at NYU and Sydney, the proposed study population is illustrated in the table below:*

|  | **Race/Ethnicity** | | | | | |
| --- | --- | --- | --- | --- | --- | --- |
| **Gender** | White, not of Hispanic Origin | Black, not of Hispanic Origin | Hispanic | Asian or Pacific Islander | Unknown | Total |
| Male | 55% | 0 | 2.5 | 2.5 | 0 | 60% |
| Female | 35% | 0 | 2.5 | 2.5 | 0 | 40% |
| Total | 100% | 0 | 0 | 0 | 0 | 100% |

**4. TREATMENT PLAN**

**4.1** Patients will be stratified based on whether or not their tumors contain a B-RAF mutation. We will obtain either real time biopsies or paraffin embedded tissue from a previous biopsy for prospective identification of the B-RAF mutation.

**4.1.1 Agent Administration**

Treatment will be administered on an outpatient basis. Expected adverse events and appropriate dose modifications for BAY are described in Section 5. No investigational or commercial agents or therapies other than those described below may be administered with the intent to treat the patient’s malignancy.

All patients will keep a drug diary in order to record compliance with their drug regime.

(See Appendix H)

###### 4.1.2 BAY 43-9006

All patients will receive:

**BAY 43-9006 (NSC 724772) 400 mg po BID over 4 weeks.**

This dose may subsequently be reduced for individual patients, depending on toxicity (Section 5.2).

In order to study the effects of BAY 43-9006 on BRAF and on other components of the pathway, we will perform pretreatment and post-treatment tumor biopsies in the first 13 patients of each subgroup. The biopsies, which will be performed in the outpatient facility, will be either punch biopsies (6-8 mm diameter) or excisional biopsies performed by a surgical member of the Melanoma Disease Management team. The first portion of the biopsy will be used to evaluate the B-RAF status of the patient. Another portion of the tissue will be preserved in formalin and submitted to the NYU Department of Pathology. This material will be used to confirm the presence of melanoma and will be used for the immunohistochemical analyses of phospho-MAPK and cyclin D1 expression. The remaining portion will be trimmed of fat and excess connective tissue, and snap frozen in liquid N2. This material will be used for the Western blot analyses.

